### Behavioral measures

#### Dietary intake

Dietary intake is assessed at baseline, six months, and 12 months using 24-hour recalls on two random days over a week [101-103], and completed using the NCI Automated Self-Administered 24-hour recall ((ASA24). The primary variables of interest are: calories, protein, carbohydrates, and fat; consumption of sugar-sweetened beverages; and consumption of fast food. Under-reporting will be estimated by comparing reported energy intakes (based on 24-hour recalls) with estimated total energy expenditure (TEE) for pregnant women [104]. If indicated, analyses will exclude extreme under-reporters. Fast food consumption is also assessed based on self-report questions used in our previous research [105].

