#### Sample size calculation

The targeted sample size (12 clinics; 34 participants per clinic; total N = 408) is projected to provide ≥80% power to detect a meaningful difference in weight change at 12 months as small as 2 kg between group means, when the standard deviation is 4.5 kg and the intraclass correlation (ICC) is 0.02, using a two-sided *t*-test with a significance level of 0.05, and accommodating anticipated rates of loss to follow-up (30% participant attrition at 12 months). Although we do not anticipate clinic attrition, 10 clinics (five in each condition) would provide 80% power to detect a difference in weight change as small as 2 kg. An ICC of 0.002 was estimated from results of our pilot demonstration trial and a WIC survey study [130], but we have conservatively used an ICC of 0.02 for sample size calculations [131]. For secondary aims, in our most conservative estimates [25], we would have greater than 80% power to detect both medium and large effects (Cohen’s d = 0.5 and 0.8, respectively) for any continuous or categorical outcome variable at the alpha = 0.05 level using a two-sided test of significance.

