#### Analysis plan

The primary outcome measure, change in weight from baseline over time, is assessed at six and 12 months. All measured weights will be included in the analyses. The analysis strategy is based on a conceptual framework that explicitly recognizes that both differences between individuals within clinics and between clinics may contribute to variance in weight change. Randomly assigned group (standard care versus intervention) is the main independent variable for intention-to-treat (ITT) analyses. County is a stratification variable for randomization and is expected to be balanced across intervention and standard care groups by design. Our analysis approach uses linear mixed-effect models to analyze differences between the intervention and standard care clinics allowing for within-cluster variation (participants within the same clinic) and within-individual variation (repeated measures) [132]. The model will include factors for a fixed effect for treatment and group and random effects for clinic as well as a group × time interaction term to test if the change over time in the dependent variable differs significantly for the two study groups. In addition, for primary and secondary outcomes, the model will include participant-level covariates to adjust for any baseline differences, or adjust for covariates that may relate to the outcome, including lactation, age, age at menarche, education, income, smoking status, language, socioeconomic status, race and ethnicity, height, pre-pregnancy BMI, parity, gestational gain, inter-pregnancy interval, baseline BMI, and changes in marital status and employment [2,133-139] In addition, the model will include terms to account for whole-clinic (cluster-level) variants, including Latina proportion, lactation proportion, mean age, mean education, and mean SES.

Our study design will give rise to temporally repeated measurements, and some subjects may be lost to follow up. In the primary analysis, missing weight measurements will be assumed missing at random, but diagnostic analyses will be conducted related to missing data (for example, comparing baseline characteristics of completers versus non-completers and creating propensity scores). If missing data appear to have the potential of influencing interpretation, we will also conduct multiple imputations using several different models for non-ignorable missingness. These will be used to assess the range of impact that missing data may exert on our results.

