A secondary aim is to test the hypothesis that the intervention will result in a greater percentage of the women achieving their preconception weight or below at 12 months. For this analysis, a generalized linear mixed-model (binomial with a logit link) will be used for proportion at preconception weight or below at six and 12 months postpartum, including the same predictors described above. For secondary analyses comparing changes in behavioral and psychosocial variables, the effect of treatment at each time point will be investigated using the same basic linear mixed-effects model described above. In analyses of the possible differential effects of treatment on various subgroups of women, interactions between patient-level covariates (as in the main analyses) and group will be examined. A Bonferroni adjustment will be used to adjust for multiple comparisons. Also, generalized linear mixed-model analyses, as described above, will also be conducted to examine whether baseline variables moderate weight loss outcomes. Analyses of whether any effect of the intervention is mediated by differences in demographic, behavioral, and psychosocial factors will be conducted by first eliminating variables that have no impact on weight loss, then variables of interest will be entered into a final linear mixed-effects model, using both theoretical considerations to guide variable selection and the statistical strength of potential predictor variables [140].

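### The model for the behavioural and psychosocial outcomes compares changes without naming each outcome's own baseline as a covariate, which is valid but gives up precision at no saving

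*Protocol article*

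**What the plan says.** The Analysis plan section of the protocol article defines one linear mixed model: a fixed group effect, random clinic effects, repeated measures within women, and a group-by-time interaction as the test of differential change. It then says that "for primary and secondary outcomes, the model will include participant-level covariates to adjust for any baseline differences", or for variables related to the outcome. A long list follows, introduced by the word including. It contains height and baseline BMI, but no baseline diet, activity, depression, stress, self-efficacy or other secondary score.

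The same section carries this model over to the secondary outcomes: "For secondary analyses comparing changes in behavioral and psychosocial variables, the effect of treatment at each time point will be investigated", using the same basic model.

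The baseline values exist. Study aims has the eating and exercise behaviours examined at 0, six and 12 months, and under Dietary intake, "Dietary intake is assessed at baseline, six months, and 12 months using 24-hour recalls on two random days over a week".

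For the secondary aims, Sample size calculation states that "we would have greater than 80% power to detect both medium and large effects" (d = 0.5 and 0.8), "at the alpha = 0.05 level using a two-sided test of significance". It does not link this to any baseline adjustment, and does not say whether d is in units of the raw-score SD or the change SD.

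**The concern.** One covariate list serves all outcomes. For weight it works, because baseline BMI and height together determine baseline weight. For calories, accelerometry or a stress scale, the list names nothing that plays this role, although the outcome's own baseline is usually its strongest single predictor.

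Putting the baseline among the repeated responses does not by itself repair this. If the two arms have free means at baseline, the group-by-time contrast is the difference in mean changes. An unadjusted change carries the noise of both measurements. It is less precise than a baseline-adjusted comparison for any rho below 1, and less precise than ignoring baseline altogether when rho is below 0.5. At stake is the width of the confidence intervals for the trial's secondary hypotheses.

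**Working it through.** **Inputs from Sample size calculation.** "12 clinics; 34 participants per clinic; total N = 408"; 30% attrition at 12 months; ICC 0.02; two-sided alpha 0.05; d = 0.5 and 0.8; for weight, 2 kg with SD 4.5 kg. Six clinics per arm is inferred from the fallback scenario of "10 clinics (five in each condition) would provide 80% power".

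**Assumptions.** rho is not given, so a range is shown. Variance is taken as equal at baseline and follow-up, and the ICC as 0.02 for raw scores and changes alike. The four crossed-over clinics, the other covariates and the Bonferroni adjustment are not modelled.

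**Step 1: effective sample size.** Completers per clinic: 34 x 0.7 = 23.8. Design effect: 1 + (23.8 - 1) x 0.02 = 1.456. Effective n per arm: 6 x 23.8 / 1.456 = 98.1.

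**Step 2: the plan's own figures.** Each result is given by normal approximation, then by a t test with clinic-level df.
- Weight, 12 clinics: 87.5% / 80.1% (10 df). The stated level of at least 80% is met.
- Weight, 10 clinics: 81.1% / 70.2% (8 df). The stated 80% matches the normal version.
- Secondary outcomes with no baseline adjustment, SD of the analysed quantity = 1: 93.8% / 88.3% at d = 0.5, and at least 99.9% at d = 0.8. The stated power above 80% is reproduced.

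**Step 3: variance of the two analyses**, in units of the raw-score variance.
- Change score: 2(1 - rho).
- Adjusted for own baseline: 1 - rho^2 = (1 - rho)(1 + rho).
- Ratio: 2/(1 + rho).

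A generalised least squares calculation (three visits, compound symmetry, complete data, one woman per arm) gave these variances for the 12-month group effect:
- Group-by-time model with free baseline means: 2.80, 2.00 and 1.20 at rho 0.3, 0.5 and 0.7. These equal the change-score values 4(1 - rho).
- Baseline means constrained equal: 1.82, 1.50 and 1.02. These equal the adjusted values 2(1 - rho^2).

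**Step 4: consequence for power at d = 0.5 if d is on the raw-score SD** (normal / t with 10 df).

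| rho (assumed) | Change variance | Adjusted variance | Ratio | Power, change | Power, adjusted |
|---|---|---|---|---|---|
| 0.3 | 1.40 | 0.91 | 1.54 | 84.1% / 76.0% | 95.6% / 91.0% |
| 0.5 | 1.00 | 0.75 | 1.33 | 93.8% / 88.3% | 98.1% / 95.3% |
| 0.7 | 0.60 | 0.51 | 1.18 | 99.5% / 98.2% | 99.8% / 99.3% |

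Unadjusted power at d = 0.5 drops below 80% only for rho under about 0.22 (normal) or 0.37 (10 df). At d = 0.8 it is 97.7% / 94.5% even at rho = 0.

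**Step 5: if d is on the change SD.** Unadjusted power is 93.8% / 88.3% whatever rho is. Adjustment raises it to between 95.8% / 91.3% (rho 0.8) and 99.1% / 97.4% (rho 0.3).

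**Step 6: size of the loss.** The share of information given up is 1 - (1 + rho)/2: 35%, 25% and 15% at rho 0.3, 0.5 and 0.7. Confidence intervals are wider by the square root of the ratio: about 24%, 15% and 8%.

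**The case against.** The strongest reply is that the omission is not definite. The covariate list is open-ended and its stated purpose is to adjust for baseline differences, so own-baseline values could be meant. A condensed article may also leave such detail to the full protocol. Part of this stands: the team may intend the adjustment. But the article does fix the model, the test and a list detailed enough to include age at menarche, and it reuses a set suited to weight where the key term no longer applies.

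A second reply is that the repeated-measures model uses the baseline as a response and is unbiased under randomisation. That is correct, and the planned analysis is not an error. It still has change-score variance unless baseline means are constrained, and the article states no constraint.

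A reader might go further in three ways that the document does not support.
- *That the claim of more than 80% power fails.* It reproduces without adjustment. A shortfall needs d on the raw-score SD together with a low rho, and neither is documented. The weight calculation uses an SD of change, and the 10-clinic figure matches the normal approximation, under which rho 0.3 still gives 84.1%. Low correlation for two 24-hour recalls is conceivable, but no figure is given.
- *That chance baseline imbalance biases the results.* The SE of imbalance is sqrt(2 x 1.66 / 204) = 0.128 SD, where 1.66 = 1 + 33 x 0.02. An imbalance of 0.2 SD or more therefore has about a 12% chance per outcome. At rho 0.5 it would shift a change score by (1 - 0.5) x 0.2 = 0.1 SD, but this is a conditional error already counted in the variance above.
- *That the mechanism analyses suffer.* They relate changes in behaviour and psychosocial factors to weight change, and these inputs are the same whichever between-arm model is used.

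**Conclusion.** The point holds as one of precision. Read literally, the secondary model is valid but less efficient than one that conditions on each outcome's own baseline, by a variance factor of 2/(1 + rho): 1.54, 1.33 and 1.18 at assumed correlations of 0.3, 0.5 and 0.7. The factor does not depend on which SD d refers to. It does rest on equal variances over time, a common ICC, complete data and no other covariates; covariates that already predict the outcome would reduce the gain.

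It is not a power failure, since the power statement for secondary aims stands at 88 to 94% for d = 0.5 on the plan's inputs. The primary analysis is not affected, because baseline BMI and height are already in that model.

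**What to change.** In the secondary-outcome paragraph of the Analysis plan, add a sentence stating that each continuous behavioural and psychosocial outcome is analysed as its six- and 12-month values, with the baseline value of that same outcome as a covariate. Alternatively, keep all three visits as responses in the repeated-measures model and constrain the baseline mean to be equal across arms. The constrained form keeps women whose baseline value is missing; the covariate form would need simple imputation of that baseline. It would also help to say in Sample size calculation which SD the d values refer to.

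The cost is a line or two of text. The baseline data are already being collected, and no further participants or visits are needed.

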### Study aims

Fit Moms/*Mamás Activas* is a cluster randomized clinical trial funded by the National Institute of Diabetes, Digestive, and Kidney Diseases (NIDDK). The clinical site is at California Polytechnic State University, San Luis Obispo ([name], Principal Investigator (PI)) and an additional performance site that is overseeing development and delivery of the online and text-messaging intervention is the University of North Carolina at Chapel Hill ([name], PI). In this cluster randomized trial, 12 WIC clinics are randomized to receive the standard WIC program for 12 months or the enhanced WIC plus internet-based postpartum weight loss program. The primary hypothesis is that the enhanced WIC plus internet postpartum weight loss program will produce significantly greater weight losses than the standard WIC at six and 12 months.

Secondary aims will determine whether the enhanced WIC plus internet postpartum weight loss program will result in greater improvements in eating and exercise behaviors (examined at 0, six, and 12 months) and psychosocial parameters (depression, social support, self-efficacy, body image, and stress) than standard care. The study will examine the proportion of women who achieve pre-pregnancy weight at six and 12 months and identify baseline characteristics that may moderate the efficacy of the intervention (such as ethnicity, socioeconomic status, pre-pregnancy weight, parity, and breastfeeding status). The study will also examine the relationship between changes in behaviors, psychosocial factors, and weight changes during the 12-month period. These evaluations will help identify the mechanisms by which the intervention produces greater success compared to the standard WIC.

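### Secondary analyses use single-step Bonferroni, which is valid; Holm's step-down gives the same familywise guarantee and never rejects less, for a gain of about 0 to 15 points of power per real effect

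*Protocol article*

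**What the plan says.** The Analysis plan of the protocol article has one sentence on multiplicity: "A Bonferroni adjustment will be used to adjust for multiple comparisons". It directly follows the plan for differential treatment effects, where "interactions between patient-level covariates (as in the main analyses) and group will be examined". Slightly earlier, the same paragraph covers changes in the behavioural and psychosocial variables. The sentence does not say whether it reaches back to those.

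Study aims names five psychosocial outcomes on which the intervention is expected to do better: "psychosocial parameters (depression, social support, self-efficacy, body image, and stress) than standard care". It gives five example moderators: "such as ethnicity, socioeconomic status, pre-pregnancy weight, parity, and breastfeeding status". The Analysis plan lists about 17 participant-level covariates that could enter interactions.

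The Sample size calculation puts the primary test at an unadjusted level ("using a two-sided *t*-test with a significance level of 0.05") and claims more than 80% power for medium and large secondary effects "for any continuous or categorical outcome variable at the alpha = 0.05 level using a two-sided test of significance".

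**The concern.** Bonferroni compares every p-value with 0.05/m. Holm compares the smallest with 0.05/m, the next with 0.05/(m − 1), and so on, stopping at the first failure. Both hold the familywise error at 0.05 or below with no assumption about dependence. Holm's first threshold equals Bonferroni's and its later ones are looser, so it can only add rejections.

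The secondary aims ask which behaviours and psychosocial factors respond and which women benefit. With 12 clinics, power for such questions is limited. If several hypotheses in a family are false, as the psychosocial aim predicts, the single-step rule gives up some power that the same error guarantee would allow.

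**Working it through.** **1. The plan's own figure.** Inputs from the Sample size calculation: "12 clinics; 34 participants per clinic; total N = 408", ICC 0.02, SD 4.5 kg, 30% attrition, and "a meaningful difference in weight change at 12 months as small as 2 kg between group means". I assume six clinics per arm and ignore the four crossed-over clinics.
- Retained per clinic: 34 × 0.7 = 23.8. Per arm: 6 × 23.8 = 142.8.
- Design effect: 1 + (23.8 − 1) × 0.02 = 1.456.
- Effective n per arm: 142.8 / 1.456 = 98.1.
- Noncentrality for 2 kg: 2 / (4.5 × √(2/98.1)) = 3.11.
- Power at two-sided 0.05: 87.5% (normal) or 80.1% (t, 10 df). The stated figure of at least 80% reproduces. It does not involve the multiplicity rule.

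**2. Validity of Bonferroni.** With m independent true nulls, the familywise error is 1 − (1 − 0.05/m)^m. This is 0.0490 for m = 5 and 0.0488 for m = 17. Unadjusted, it would be 1 − 0.95^5 = 0.226 and 1 − 0.95^17 = 0.582. Bonferroni does its job. In simulation with every null true, Holm has the same error (0.0491 for both at m = 5; 0.0496 for both at m = 17).

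**3. Subgroup interactions.** The number of tests is not given, so I take m = 5 (the example moderators) to m = 17 (the covariate list). Assumptions: independent tests, and 80% unadjusted power for each real interaction; 200,000 runs.

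| m | Real | Bonferroni, power per real effect | Holm |
|---|---|---|---|
| 5 | 1 | 59.1% | 59.3% |
| 5 | 2 | 59.0% | 60.9% |
| 5 | 5 | 58.9% | 70.4% |
| 17 | 1 | 43.2% | 43.3% |
| 17 | 2 | 43.1% | 43.4% |
| 17 | 8 | 43.2% | 45.8% |
| 17 | 17 | 43.2% | 52.1% |

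With one or two real interactions the gain is at most 1.9 points. A variant with m = 17, correlation 0.3, noncentrality 2.8 and 250 df gives gains of 0 to 1.4 points for one to five real interactions. The rows where every interaction is real are shown only as a limit.

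**4. Five psychosocial outcomes, if the sentence covers them.** I assume d = 0.5 and that ICC 0.02 and 30% attrition apply to these outcomes. The noncentrality is 0.5 / √(2/98.1) = 3.50. On 10 df, power is 88% at 0.05 and 63% at 0.05/5 = 0.01. The simulation uses correlation 0.3 and 10 df. It was run with one variance estimate shared by all outcomes and again with independent ones, because the document does not settle this.

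| Real of five | Bonferroni | Holm, shared variance | Holm, independent variances |
|---|---|---|---|
| 1 | 63% | 63% | 64% |
| 3 | 64% | 68% | 69% |
| 5 | 63% | 76% | 79% |

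The gain is near zero with one real effect, about 5 points with three (4.8 and 5.7), and about 12 to 15 with all five.

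**5. What does not change.** The methods part company only after a first rejection, so the chance of at least one rejection is identical (for example 60.8% for both at m = 5 and 45.9% for both at m = 17, one real effect, settings of step 3). No run had Bonferroni rejecting where Holm did not.

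**6. What Holm costs.** With three of five real in step 4, the chance of a false rejection among the two true nulls rises from about 2% to about 4%. That is still within 5%.

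**The case against.** The strongest reply is that Bonferroni is a standard, valid rule, fixed in advance and contradicted by nothing in the article, so preferring another valid rule is a matter of taste. Validity is conceded in full. What remains is that the alternative is uniformly at least as powerful under the same guarantee and costs one line. That makes this an optional improvement.

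Other parts of the reply also stand:
- The position of the sentence points to the subgroup interactions, where the gain is small. The larger gains need both a wider reading of the sentence and several psychosocial outcomes responding together.
- Bonferroni does buy something: one fixed threshold and simple simultaneous intervals that match the tests. The article does not say that it will report such intervals, but the advantage is real.
- Part of Holm's extra power comes with a higher realised error on true nulls, within the same bound.
- Correlation among the covariates or scales is no argument for Holm. Neither procedure uses it, and both are conservative when it is positive.

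A reader might go further and infer that the claimed secondary power of more than 80% is wrong, because it is computed at 0.05 and not at an adjusted level. The article does not support that. It does not say the adjustment governs those outcomes. Even if it did, power for d = 0.5 at 0.01 is 63% on 10 df but 82% with large df, so the answer turns on an unstated choice.

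**Conclusion.** The point holds as a minor, optional improvement. The protocol article fixes a valid rule where a uniformly at least as powerful one exists under the same familywise 0.05 guarantee. The likely gain is about 0 to 2 points per real effect if only interactions are covered and few are real. The figures of about 5 and 12 to 15 points apply only if the five psychosocial outcomes are covered and three or all five respond, under the assumed d, ICC, attrition, degrees of freedom and correlation. Of these, the article gives d = 0.5, the ICC and the attrition in its power statements. The correlation, the 10 df and the number of tests are assumptions.

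It would be wrong to conclude that Bonferroni is an error here, that it brings no benefit, or that the trial will broadly miss real effects. The chance of finding at least one is unchanged, and the primary analysis and its stated power are untouched.

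**What to change.** Replace the Bonferroni sentence with, for example: *Holm's step-down procedure at familywise 0.05 will be used to adjust for multiple comparisons.* Apply it to exactly the set of comparisons the present sentence was meant to cover. Splitting that set into separate families, each at 0.05, would alter the scope of error control and is a different decision.

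The cost is one line, made before the data are analysed, with no new software or data. Holm has no simple matching simultaneous intervals. If simultaneous intervals are wanted, Bonferroni intervals can be reported alongside, with a note that an interval may include no effect where Holm rejects.

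### The mediation procedure selects predictors of weight loss without tying them to the intervention's effect on each factor, and it counts demographics among the mediators

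*Protocol article*

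**What the plan says.** The Analysis plan section of the protocol article states a mediation procedure. Whether an intervention effect is "mediated by differences in demographic, behavioral, and psychosocial factors will be conducted by first eliminating variables that have no impact on weight loss" is the first step. The variables of interest then go into a final linear mixed-effects model, "using both theoretical considerations to guide variable selection and the statistical strength of potential predictor variables".

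Three other statements bear on this:

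- Earlier in the same paragraph of the Analysis plan: "For secondary analyses comparing changes in behavioral and psychosocial variables, the effect of treatment at each time point will be investigated", with the same basic mixed model as the main analysis.
- Study aims, on purpose: "These evaluations will help identify the mechanisms by which the intervention produces greater success compared to the standard WIC".
- Study aims, on baseline traits: the study will "identify baseline characteristics that may moderate the efficacy of the intervention (such as ethnicity, socioeconomic status, pre-pregnancy weight, parity, and breastfeeding status"). The Analysis plan provides for this moderator analysis separately, in the sentence just before the mediation one.

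**The concern.** A mediator has to meet two conditions: the intervention changes it, and that change in turn affects weight given group. The written screen looks only at the link with weight loss. A woman's score on some scale may predict her weight loss equally well in both arms; such a factor passes the screen, can be strong in the final model, and says nothing about how the intervention works.

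The candidate list adds a second problem. Fixed demographic traits cannot lie on a path that starts at randomization, and the Study aims already give several of them the role of moderator.

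At stake is the mechanism aim. The Discussion expects later research to separate the contributions of the levels of the intervention package, and a correlate reported as a mechanism would misdirect that work.

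**Working it through.** **No stated figure to reproduce.** The plan gives no number for the mediation analysis. The primary power claim was checked in passing: 6 clinics per arm, 34 × 0.7 = 23.8 completers per clinic, design effect 1 + 22.8 × 0.02 = 1.456, noncentral t with 10 degrees of freedom. This gives 80.1% against the stated 80% or more. It has no bearing on this point.

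**Step 1. Conditions for mediation against the text.**

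| Needed for mediation | In the mediation step | Elsewhere in the Analysis plan |
|---|---|---|
| Group changes the factor | Not mentioned | Tested for behavioral and psychosocial variables, but not linked to the mediation step |
| Factor affects weight given group | Screen on weight loss, then final model; the text does not settle whether group is in that model | – |
| Indirect effect, or group effect with and without the factor | Not mentioned | Not mentioned |

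**Step 2. Demographics.** Supporting measures records age, race and ethnicity at baseline. Study aims names ethnicity, socioeconomic status and parity as possible moderators. The mediation sentence nevertheless lists demographic factors as mediators.

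**Step 3. How easily a non-mediator passes the screen (illustration).**

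- From the Sample size calculation: 408 women and 30% attrition, so 408 × 0.7 = 285.6, about 286 completers.
- Assumed: a two-sided 0.05 screen (the plan gives no threshold), independent women, no group effect on the factor, and correlation r with weight change.
- Formula: pass probability ≈ Φ(atanh(r) × √(286 − 3) − 1.96), with √283 = 16.82.

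| r | atanh(r) × 16.82 | minus 1.96 | Pass probability |
|---|---|---|---|
| 0.15 | 2.54 | 0.58 | 72% |
| 0.20 | 3.41 | 1.45 | 93% |
| 0.25 | 4.30 | 2.34 | 99% |

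As a rough allowance for clustering, divide the sample by the full design effect: 286 / 1.456 = 196.4 and √193.4 = 13.91. The pass probabilities become about 56%, 80% and 94%. In every row the true indirect effect is zero.

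**Step 4. Does a test of both paths separate the cases?** This used 2,000 simulated trials per case, 286 women and no clustering. The path values are assumptions in units of the residual SD: *a* is the group effect on the factor, *b* the factor's effect on weight given group. The total group effect is 0.44 (2 kg / 4.5 kg) in each case. The final model is assumed to include group.

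| Case | Passes screen | Significant in final model | Both paths significant |
|---|---|---|---|
| Predictor, not mediator (a = 0, b = 0.4) | 100% | 100% | 4.3% |
| True mediator (a = 0.5, b = 0.4) | 100% | 100% | 98.4% |
| Moved by the intervention, no effect on weight (a = 0.5, b = 0) | 14% | 5.1% | 5.1% |

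The screen and final model largely reject the third case. They treat the first two alike, and telling those two apart is what the mechanism aim requires.

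**The case against.** The strongest reply is that much of what is needed is already in the plan. The group effect on behavioral and psychosocial variables will be estimated, so for those candidates half of the path is available. This stands. A reader might infer that the path from group to mediator is never examined; the Analysis plan does not support that. The fault is that the mediation step neither draws on those estimates nor forms an indirect effect.

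Theory also guides selection, and the Background sets out social cognitive theory as the basis. This stands too: prediction is not the only criterion. But theory can nominate a candidate; it cannot show that the intervention moved it.

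A reader might also infer that no demographic factor can ever mediate. That is too strong. The Analysis plan lists changes in marital status and employment as covariates, and job status is assessed at follow-up. These can change after randomization, so the objection is to fixed traits.

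The Study aims say only that these evaluations will help identify mechanisms, and they include the modest goal of relating changes in behavior and psychosocial factors to weight change. It would be wrong to infer that the aim is wholly out of reach: the planned models can describe those associations. They cannot, as written, support a claim of mediation.

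Finally, the article cites a source for its method, and neither that source nor any separate analysis plan is at hand. The choice of estimator may properly be left to them. The point here is the selection rule and candidate list that the article does state; an analysis plan that followed them would inherit the fault.

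**Conclusion.** The point holds as a flaw in a stated secondary method. The procedure selects on association with weight loss, together with theory, and does not connect that selection to the group effects on the same factors or to an indirect effect. The demographic entry is wrong for fixed baseline traits and conflicts with their role as moderators in the Study aims.

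The size can only be illustrated. The 72%, 93% and 99% rest on an assumed 0.05 screen, assumed correlations and independent women; the simulation rests on assumed path values. They show how often a factor with no indirect effect would pass the first step, not how often it would be reported as a mechanism, since theory and a final model follow. The logical point does not depend on these numbers. The primary weight comparison is not affected, and the change is worth making before the mechanism analysis is run.

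**What to change.** Amend the mediation text in four respects:

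1. Keep fixed demographics as covariates or moderators only.
2. Drop the screen on weight loss and name the behavioral and psychosocial candidates in advance, on the theory the article already sets out.
3. For each candidate, take the planned group effect on its change from baseline to six months, and estimate the effect of that change on 12-month weight with group in the model. This places the mediator before the outcome.
4. Report the indirect effect with a confidence interval that allows for clinic clustering.

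The mediator is not randomized, so the second path should also adjust for baseline covariates, and the report should say that it assumes no unmeasured confounding between mediator and weight.

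The cost is revised wording and modest extra analysis and programming. Behavioral and psychosocial measures at baseline, six and 12 months are already planned, so no new data are needed.
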